### Blinding

This study will implement a complete separation of treatment and assessment to allow for a single blind design of assessment. Therefore, therapists will not be involved in the assessment of the treatment outcome, and raters will not be allowed to hold treatment sessions. Patients will be informed about their treatment allocation by the therapist, and only therapists will receive information about group allocation. Discussions about patients enrolled in the study will be not allowed between raters and therapists, as per instructions given during staff training.

The raters will have to complete a ‘blindness protocol’ at the end of the study. Any unintentional disclosure of the treatment condition will therefore be hopefully documented. Further, the raters will be asked to guess the study condition of the patient after the end of the study. Among all documented guesses, the rate of correct guesses should not significantly differ from chance (that is, 50%). The main outcome of the study is adherence to the prescribed therapy, and one of the indicators is the measurement of blood levels of the primary prescribed drug, which is independent from the assessment carried out by the raters. It is unlikely that any personal opinion of the raters on the presumed superior effectiveness of the FPP over GT will influence the measurement of blood levels of the primary prescribed drug. However, we are interested in knowing whether any bias might have occurred in the blinding, whether by unintentional disclosure of the treatment condition or because the personal opinion of the raters led them to guess the patients’ allocation to the treatment modality.

### Planned interventions

The FPP aims at improving communication and problem-solving abilities in patients and their families through sessions focused on: assessment of the individual’s and the family’s strengths, weaknesses, and goals; education about schizophrenia and treatment; communication skills training; problem-solving training; and training to cope with special problems [19]. Treatment sessions are provided on a weekly basis for six months (one and a half hours for each session). The first six sessions will be provided to each individual family with the participation of the patient and the caregivers, while the following sessions up to the 18th will be provided to clusters of families, according to a multi-family revised version of family psychoeducation [28,29].

The GT is a treatment providing general information on the disorders and with the same frequencies as the FPP (Table 2). The GT treatment sessions are also provided on a weekly basis for six months (one and a half hours for each session). Each GT session is structured in three steps: first, a short (20 minutes maximum) and hopefully informative introduction on selected topics concerning the main problems related to the disorder (see Table 2 for details); then family members are asked to discuss whether and how they faced the problem described, whether the solution was effective and why, and they are then are invited to imagine alternative solutions to the problem that differ from the solutions they adopted; finally, a ten-minute conclusion summarizes the main elements of the topic discussed during the meeting. This scheme is specifically effective in multi-family meetings, when different families are invited to discuss and compare the problems they faced and the solutions they adopted, and whether effective or not.

**Table 2 T2:** Timing and structure of the planned interventions: Falloon and co-workers’ Psychoeducation Program (FPP) and Generic Treatment (GT)

**Sequence**	**Month**	**FPP**	**GT**	**Type of meeting**
1 week	1	Introduction	Introduction on schizophrenia	Single family
2 week	1	Evaluation of individual family members	Meeting on delusions, hallucinations and apathy	Single family
3 week	1	Whole family evaluation	Meeting on depression, shame and risk of suicide	Single family
4 week	1	1. Informative meeting on schizophrenia	Meeting on drugs	Single family
5 week	2	2. Meeting on drugs	Meeting on aggressive behavior	Single family
6 week	2	3. Meeting on early signs of relapse	Meeting on psycho-social treatments	Single family
7 week	2	Practical problem solving 1	Meeting on free time, leisure and school	Multi-family
8 week	2	Practical problem solving 2	Meeting on participation in family life	Multi-family
9 week	3	Practical problem solving 3	Meeting on early signs of relapse	Multi-family
10 week	3	Interpersonal problem solving 1	Meeting on eating habits and obsessions	Multi-family
11 week	3	Interpersonal problem solving 2	Meeting on therapy acceptance	Multi-family
12 week	3	Interpersonal problem solving 3	Meeting on self-care and somatic health	Multi-family
13 week	4	Personal problem solving 1	Meeting on disability	Multi-family
14 week	4	Personal problem solving 2	Meeting on stigma	Multi-family
15 week	4	Personal problem solving 3	Meeting on legal problems and substance abuse	Multi-family
16 week	4	First verification of family changes	Meeting on social anxiety	Multi-family
First week of the month	5	Second verification of family changes	Meeting on social services	Multi-family
First week of the month	6	Third verification of family changes	Summary meeting and verification of family changes	Multi-family

Both treatments share some common, non-specific effects, while they differ on their specific effects. The basic strategy in family psychoeducation attempts to reduce the impact of environmental stress on biologically vulnerable individuals by promoting communication within the family, increasing coping skills and improving problem-solving abilities [30]. These outcomes are expected to be produced by: a) providing information about the disorder, which should also decrease the pathogenic impact of ‘false myths’ concerning the illness; b) the provision of coping strategies to manage crises; c) the implementation of a more comfortable environment where support is provided by peers and professionals. Within this framework, non-specific effects include emotional support, empathic listening, and the implementation of therapeutic optimism. Specific effects, expected to influence therapeutic outcome, are thought to be the consequence of specific and well-defined treatment strategies. In the FPP, the specific effects are thought to be the consequences of improved problem-solving, better coping and tolerance to stress, and improved social skills acquired by the intervention. In the GT, the specific effects are essentially the reduction of shame and sense of guilt obtained by explicitly talking about situational problems related to the disorder, and the modelization on the non-judgmental, empathic and supportive behavior of the therapist.

For both the FPP and GT, participation in the meetings by each family member who has expressed willingness to participate will be recorded. A family will be considered adherent to the psychoeducation treatment when at least one member of the family has participated in 70% of the meetings (n = 12 out of 18). The rate of family attendance will be considered as a confounding variable in the evaluation of outcome. Percentage of drop-out by type of psychoeducation treatment (families who have not participated in three successive meetings and have not attended at least 70% of meetings overall) will be considered as an independent measure of applicability of the method (FPP or GT).

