### Recruitment and baseline procedures

Patients will be enrolled in the clinical setting, which includes both GHPUs and UPCs.

To rationalize the training and quality-control procedures for the FPP and GT therapists (two for each participating unit) and the assessors (one for each unit), a Training and Quality Control Center will be established in Cagliari, the site of the coordination unit. This Center will train the assigned therapists in FPP and GT and will also train the assessors in the administration of the psychometric measures. On a regular six-month basis, the Center will organize meetings to verify the course of the study.

The Coordination Center will manage the procedures of treatment allocation and will coordinate the study, the statistical analysis, the storage of data, the training of the assessors involved in the patients’ evaluation and of the therapists involved in the FPP and GT. The Coordination Center with two units from the University of Cagliari (Center for Research and Treatment in Mental Health and Pharmacological Unit) will monitor data recording and storage, quality assessment of FPP and GT, and quality assessment of the training for assessors and therapists.

A Steering Committee (the principal investigator plus another member of the Coordination Center, a member from the Monitoring Unit, a member from the Statistics Unit, and three members elected by the enrolling units) will coordinate the use of the database for publications. A centralized laboratory (Pharmacological Unit, University of Cagliari) will analyze the blood levels for drugs in the samples received from all participating units.

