### Sample size and power

Sample size for the identification of the expected difference in the primary outcome (adherence to pharmacotherapy) was based on known evidence: prevalence of non-adherence to pharmacotherapy in patients already in contact with a psychiatric service is around 40 to 50%, median = 47% [11,12]; effect size of psychosocial treatment on various outcomes, including relapse, readmission and adherence to pharmacotherapy is 0.48 of the standard deviation (SD), with 95% CI= 0.10 to 0.85 [16]. We expect that our intervention could produce a change in the prevalence of non-adherence to pharmacotherapy in the exposed group with an effect size of 0.45 SD [11,12]. After performing a test of difference between proportions we determined that a sample of 78 participants per group would be needed to achieve 80% power to detect a difference with h = 0.45 (medium effect size) in the measures of adherence to pharmacotherapy, at a two-sided significance level of 0.05 and allocation ratio of 1:1.

Cohen’s h effect size for the difference of proportions is calculated on the formula:

$$h=2^{*}\arcsin\;p1-2^{*}\arcsin\;p2$$

where p1 and p2 are the proportions of adherent patients in the exposed group 1 and the non-exposed group 2, respectively [59]. The Cohen’s h measures the same effect size interval as the Cohen’s d but is based on differences by proportion rather than by continuous variables [59].

Cohen’s h = 0.45 implies that at the estimated power (= 80%) we can observe a 25.5% rate of non-adherence to pharmacotherapy in the exposed group as opposed to a 47% rate in the unexposed group. In this case, risk reduction is 0.215, corresponding to a number needed to treat (NNT) = 5. Since we do not know the exact proportion of non-adherence, here are the different starting p1 and related maximum p2 detectable:

p1: 0.65 0.60 0.55 0.50 0.45 0.40 0.35 0.30 0.25

p2: 0.43 0.38 0.33 0.28 0.24 0.20 0.16 0.12 0.09

Since this a multisite study, the clusterized nature of the data has to be controlled since it has an impact on an unequal variance by center, which requires a correction of the sample according to the formula:

$$\mathrm{DE}=1+\left(m-1\right)\times r$$

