where m is the original sample size per cluster (in our study, m = 7.8 + 7.8 = 15.6 about 16), r is a value summarizing the intra-cluster correlation coefficient (ICC), and DE (design effect) is the correction needed to maintain the same effect size in the expected change produced by the treatment [60]. In most studies, the ICC varies between 0.02 and 0.05. With ten enrolling units, precautionary ICC equals 0.05 and DE 1 + (16–1)*0.05 = 1.75. Therefore, by multiplying the initial sample size (n = 156) by DE, the final ICC-corrected sample size is 273, equal to 27.3 about 28 patients per cluster.

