### Data management and analysis

All analyses will be based, as far as possible, on the intention-to-treat principle. Differences in the primary outcome (adherence to pharmacotherapy) will be analyzed with a two-tail test for proportions with the Miettinen exact test [61]. A multiple logistic regression will be carried out to control for the confounding variables [62] using adherence (yes/no) as the outcome to verify the impact of the FPP on controlling the impact of the confounding variables (sex, age, severity of the disorder, cluster).

Survival analyses will be performed using the Kaplan-Meier method, followed by the log-rank test to define the terminal events at both the start of non-adherence and the first relapse or readmission episode [63]. Intention-to-treat will be applied considering the primary and secondary outcomes [64]. Multiple imputations will be applied to integrate missing data [65].

As far as validation of the self-report (MARS) and the interview (BARS) measure of adherence with respect to the blood levels of the main prescribed drug is concerned, Spearman’s rho will be used to compare blood levels of the main drug with the self-report or the interview; partial correlation will be used to ascertain the links between blood levels of the main drug with the self-report or the interview by taking into account the other measures (the interview or the self-report, respectively).

All analyses will be done with Excel (Microsoft Excel 2013 running on Windows 8) (Chicago, IL 60606, USA) or the Statistical Package for Social Science (SPSS) version 17 for Windows.

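### Two-thirds of the sessions run in multi-family groups within an arm, but the primary test and log-rank test treat patients as independent, so type I error may exceed 5% if outcomes correlate within groups

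*Protocol article*

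**What the plan says.** Under Planned interventions, the first six sessions are held with each family separately; then "the following sessions up to the 18th will be provided to clusters of families". Table 2 marks sessions 7 to 18 as multi-family in both arms and gives the arms different content, so a therapy group belongs to one arm. Under Recruitment and baseline procedures, staffing is described as "FPP and GT therapists (two for each participating unit"), with no statement of how the two are divided between FPP and GT. Patients are randomised individually, stratified by location, and every unit contributes to both arms (Randomization procedures).

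Under Sample size and power, the one source of clustering named is the centre: "Since this a multisite study, the clusterized nature of the data has to be controlled". Under Data management and analysis, the primary outcome is compared by a two-tailed test of proportions (a Miettinen exact test), and the time-to-event outcomes by Kaplan-Meier curves and a log-rank test. A multiple logistic regression follows, "controlling the impact of the confounding variables (sex, age, severity of the disorder, cluster"). The sample-size section uses the word cluster for the enrolling unit. Neither therapy group nor therapist is named as a source of correlation.

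**The concern.** Families who meet together for 12 sessions can become more alike in outcome than families in other groups of the same arm. The article's own account of the mechanism points this way: it credits peer and professional support, and says that the GT format works particularly well when families compare solutions.

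This correlation arises inside an arm, so it passes into the treatment contrast. A term for enrolling unit removes what the two arms of a unit share, but not what is specific to one arm's group. A larger sample does not correct the standard error of a test that assumes independence. At stake are the true error rate of the primary comparison and the width of its interval, in a trial whose positive result is meant to support use of FPP throughout the Italian NHS.

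**Working it through.** **Inputs from the article.** Planning is "at a two-sided significance level of 0.05 and allocation ratio of 1:1", and "a sample of 78 participants per group would be needed to achieve 80% power to detect a difference with h = 0.45". The rates are given as "we can observe a 25.5% rate of non-adherence to pharmacotherapy in the exposed group as opposed to a 47% rate in the unexposed group". There are ten units, 340 patients are enrolled, and drop-out is 20%. For the intraclass correlation (ICC): "In most studies, the ICC varies between 0.02 and 0.05".

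**Reproducing the plan.**
- n per arm = 2 × ((1.96 + 0.842)/0.45)² = 77.5, so 78.
- h for 47% against 25.5%, with the arcsine of the square root, is 0.452.
- Centre design effect = 1 + (16 − 1) × 0.05 = 1.75, and 156 × 1.75 = 273.
- 273/0.80 = 341, which matches 340 closely.

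**Assumptions.** 340 × 0.80 = 272 evaluable, or 136 per arm. The centre ICC range is applied to therapy groups. Group size m is 272/20 = 13.6 with one group per arm per unit, 272/40 = 6.8 with two, or 4 to 5 for small groups.

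**Formulas.** Design effect DE = 1 + (m − 1) × ICC. The standard error is too small by a factor √DE. True two-sided error = 2 × (1 − Φ(1.96/√DE)). Power = Φ(0.45 × √(136/(2 × DE)) − 1.96).

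| m | ICC | DE | √DE | True error | Power |
|---|---|---|---|---|---|
| 4 | 0.02 | 1.06 | 1.03 | 5.7% | 95% |
| 4 | 0.05 | 1.15 | 1.07 | 6.8% | 93% |
| 5 | 0.02 | 1.08 | 1.04 | 5.9% | 95% |
| 5 | 0.05 | 1.20 | 1.10 | 7.4% | 92% |
| 6.8 | 0.02 | 1.12 | 1.06 | 6.4% | 94% |
| 6.8 | 0.05 | 1.29 | 1.14 | 8.4% | 90% |
| 13.6 | 0.02 | 1.25 | 1.12 | 8.0% | 91% |
| 13.6 | 0.05 | 1.63 | 1.28 | 12.5% | 83% |

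A beta-binomial simulation of the normal-approximation test (20,000 runs, ten groups of 14 per arm, rate 0.47) gave 4.9% at an ICC near zero, 7.8% at 0.02 and 12.6% at 0.05.

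**Offset from centre variance.** Randomisation is stratified by centre but the test of proportions is not. The naive variance therefore keeps centre variation that cancels from the true contrast. The ratio of true to naive variance becomes 1 + (m − 1) × ICC_group − ICC_centre.
- For m = 13.6 and ICC_centre = 0.05, the ratio is 1.20 at a group ICC of 0.02 and 1.58 at 0.05. The true errors are 7.4% and 11.9%.
- For m = 4 and ICC_centre = 0.05, the ratios are 1.01 and 1.10. The true errors are 5.1% and 6.2%.
- The break-even group ICC is 0.05/12.6 = 0.004 for m = 13.6 and 0.05/3 = 0.017 for m = 4.

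**Exact test.** Fisher's test was simulated as a stand-in (136 per arm, rate 0.47), because the cited Miettinen procedure cannot be checked here and may be less conservative. It gave 3.3% with no clustering. Groups of 4 gave 4.2% (ICC 0.02) and 5.0% (ICC 0.05). Ten groups of 13 or 14 per arm gave about 6% and 10%.

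**The case against.** The strongest reply is that the size is conditional throughout. The article gives no therapy-group ICC; 0.02 to 0.05 is its range for centres. It gives no group size. One group of 13 or 14 families is large for a 90-minute GT session: after up to 20 minutes of introduction and 10 of conclusion, 60 minutes remain, about 4.4 minutes per family. With small groups, the exact test and the leftover centre variance together could absorb the excess. All of this stands, and it limits the size of the point.

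A second reply is that clustering has been handled: the sample carries a design effect of 1.75, the logistic model includes cluster, and attendance at meetings is recorded. The first part stands for power, since 1.75 exceeds the 1.63 found for one group per arm per unit. It does not stand for type I error, because neither the inflation nor a unit term corrects the standard error for correlation inside one arm.

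A third reply is that random effects and small-sample corrections belong in an analysis plan that is not shown. That is fair for the detail. However, the article itself names the primary test, and the one that it names assumes independence although the delivery it describes is in groups.

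A reader might also infer that families in an arm share a therapist, so that therapist effects are nested in arm. The article does not say so. If both therapists in a unit deliver both treatments, their main effects largely cancel from the contrast.

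**Conclusion.** The point holds in conditional form. The article fixes group delivery for 12 of 18 sessions and an independence-based primary test and log-rank test, and nothing that it states corrects for correlation specific to a therapy group within an arm. If that correlation is positive and not negligible, inference is anti-conservative.

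For a normal-approximation test, with the borrowed ICC range and 272 evaluable patients, true two-sided error is about 8% to 12.5% with one group per arm per unit and about 6% to 8% with two. With groups of four or five it is about 6% at an ICC of 0.02 and about 7% at 0.05, closer to 5% to 6% in groups of four if the centre ICC is 0.05. A conservative exact test would lower every figure.

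Two stronger readings are not supported. Standard errors cannot be called too small outright, because the group ICC is unknown. Nor does the documented design imply power below 80%: a figure of 79% arises only by pairing groups of 17 (all 340 patients in 20 groups) with 272 evaluable patients. Consistent inputs give 83%.

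**What to change.** Record for each patient the multi-family group attended and the therapist or therapists who led it. State how therapists are divided between arms and the intended group size.

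Make the primary comparison a model with enrolling unit as stratum and either a random intercept or a cluster-robust variance for therapy group within unit-by-arm. Apply a small-sample correction, since there may be only about 20 groups. Where a unit runs one group per arm, unit-by-arm is the cluster. Use a matching cluster-robust approach for time to non-adherence, relapse and readmission. Restate the clustering allowance in the sample-size section on the therapy group.

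The cost is an identifier or two on the case report form, best captured as groups form because it may be hard to recover later, and revised analysis wording. Intervals will be somewhat wider. On the assumptions above, power for h = 0.45 with 272 evaluable and one group per arm per unit is 83% to 91%, against 96% under independence, so no increase in sample size is needed.

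### The family-adherence cut-off equates 70% of 18 meetings with 12, but 12 of 18 is 66.7%; a family at exactly 12 meetings can be both adherent and a drop-out

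*Protocol article*

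**What the plan says.** All the relevant text is in the protocol article, Planned interventions.

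- **Adherent family.** A family is adherent "when at least one member of the family has participated in 70% of the meetings (n = 12 out of 18".
- **Drop-out.** Drop-outs are "families who have not participated in three successive meetings and have not attended at least 70% of meetings overall". This rule gives a percentage and no count.
- **Number of meetings.** The first six sessions are for single families, "while the following sessions up to the 18th will be provided to clusters of families". Table 2 lists the same 18.
- **Use of attendance.** The text states: "The rate of family attendance will be considered as a confounding variable in the evaluation of outcome". The percentage of drop-outs by type of treatment "will be considered as an independent measure of applicability of the method (FPP or GT".

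**The concern.** The percentage and the count in the adherence definition do not describe the same cut-off. The mismatch is one meeting wide, but in a classification rule one meeting decides the class. The 70% figure then returns without a count in the drop-out definition. An analyst who treats 12 as the working form of 70% and one who computes the percentage will classify families at exactly 12 meetings differently.

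What is at stake is the comparison of drop-out between FPP and GT. The Aims section sets out to evaluate the feasibility of FPP in standard care. The Discussion considers preferring GT if the two prove equally effective. A between-arm applicability figure could inform that judgement, so its threshold should not be left to be settled once attendance is known.

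**Working it through.** **Inputs.** Threshold 70% and count 12 of 18 (adherence definition); threshold 70% plus three successive absences (drop-out definition); 18 meetings (text and Table 2). I read the first limb of the drop-out rule as missing three meetings in a row.

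**Denominator.** Table 2 has 16 weekly rows and 2 monthly rows: 16 + 2 = 18. By type, 6 single-family + 12 multi-family = 18.

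**The plan's own figure.** 0.70 × 18 = 12.6.

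- Rounding up gives 13, and rounding to the nearest integer gives 13.
- Only truncation gives 12, and a truncated count does not meet a 70% minimum.
- 12/18 = 66.7%; 13/18 = 72.2%.

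The stated 12 would reach 70% with a smaller denominator (12/17 = 70.6%; 12/16 = 75.0%), but the definition itself says 18.

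**Classification around the boundary.**

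| Meetings attended | Three successive absences? | Adherent by count (≥ 12) | Adherent by percentage (≥ 70%) | Drop-out by percentage |
|---|---|---|---|---|
| 11 (61.1%) | yes | no | no | yes |
| 11 (61.1%) | no | no | no | no |
| 12 (66.7%) | yes | **yes** | no | **yes** |
| 12 (66.7%) | no | yes | no | no |
| 13 (72.2%) | either | yes | yes | no |

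Only the two rows at 12 meetings are sensitive to the discrepancy, and only the first of them puts a family in both classes.

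**Can the overlap occur?** A family with 12 meetings has 6 absences. There are C(18,6) = 18,564 ways to place them. To count the patterns with no three in a row, note that the 12 attended meetings leave 13 gaps, each holding 0, 1 or 2 absences. With j gaps holding two absences, the number of patterns is C(13,j) × C(13−j, 6−2j):

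- j = 0: 1,716
- j = 1: 13 × 495 = 6,435
- j = 2: 78 × 55 = 4,290
- j = 3: 286

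The total is 12,727. So 18,564 − 12,727 = 5,837 patterns (31.4%) contain three successive absences. This counts patterns and does not forecast behaviour, because real absences may cluster.

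One ordinary example from Table 2 is a family that attends weeks 1 to 12 and then stops. It has 12 of 18 meetings and six successive absences, so the count makes it adherent and the percentage makes it a drop-out.

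**The case against.** The strongest reply is that little depends on the count. It appears only in the definition of an adherent family, and no analysis is named for that yes/no label. The confounder is the attendance rate. Data management and analysis lists sex, age, severity and cluster as the confounders in the logistic regression, and applies intention-to-treat. The drop-out rule has its own single number and can be applied literally as written. If 12 is simply the trial's truncated working form of 70%, it could be carried into both sentences and no family would fall in two classes.

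Most of this stands and limits the point. It does not remove it: the article does not say that 12 replaces 70% in the drop-out rule, so both readings remain open, and they give different drop-out status to families at 12 meetings with three successive absences.

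Three stronger inferences are tempting, and the document does not support them.

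- **That every family at 12 meetings is put in two contradictory classes.** The drop-out rule is conjunctive, so falling below 70% is not enough without three successive absences.
- **That a number of affected families can be given by applying a share to the 340 patients.** The article gives no attendance distribution, so any such share would have no basis in it.
- **That the efficacy conclusions are at risk.** No stated primary or secondary efficacy analysis uses this cut-off.

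**Conclusion.** The point holds as a small arithmetic inconsistency in an operative rule. The stated count (12, or 66.7%) does not meet the stated percentage (70%, which needs 13).

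The consequence has two parts. Families at exactly 12 meetings with three successive absences are adherent by the count and drop-outs by the percentage, so the by-arm applicability measure depends on which figure is coded. Families at 12 meetings without such a run change only their adherent label, which has no named analysis.

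The conclusion rests on 18 meetings, which the text and Table 2 both give, and on reading the drop-out rule as requiring both conditions. The number of families involved cannot be estimated from the document. This is a minor correction, worth making because it removes a choice that could otherwise be made after attendance is known.

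**What to change.** State one integer cut-off and use it, in the same words, in both definitions. Two forms are consistent, and the sponsor should say which was intended:

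- at least 13 of 18 meetings, if 70% is meant; or
- at least two thirds of the meetings (12 of 18), replacing 70% in both places.

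Either form makes the classes mutually exclusive without a further coding rule. A member who reaches the cut-off also brings the family's attendance to it, and a drop-out family must be below it. Families below the cut-off without three successive absences will still belong to neither class, as the present rules already imply.

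The cost is a one-line edit. Participation of each willing family member is already to be recorded, so no data collection changes. The correction should be dated before attendance is summarised by arm.
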